## Data collection

The trial assessment schedule for ACT HIV is outlined in
Table 3.

**Table 3. T3:** ACT HIV trial assessment schedule.

	DAYS MONTHS										
	SCREENING	0	3	7	W eekly until discharge	30	60	M onthly to anti-TB drug end	12	18	24
ALL PARTICIPANTS											
Eligibility assessment	(X)										
Participant information sheet and consent	X										
Randomisation		X									
Clinical assessment	(X)	X	X	X	X	X	X	X	X	X	X
Disability assessment						X	X	X	X	X	X
Chest X-ray	(X)						X		X		
Lumbar puncture (with paired plasma glucose) CSF Cryptococcal Ag test	(X) (X)					X	X				
HIV test	(X)										
EDTA blood for genetic tests Full blood count CD4 count HIV viral load Storage for later DNA extraction	(X) (X)	X X X		(X)			X				
Sodium Urea/Creatinine ALT/ bilirubin Hepatitis C antibodies Hepatitis B surface antigen Fasting blood sugar/ HbA1c C-peptide/Lipids Strongyloides serology Serum Storage	(X) (X) (X)	X X X X X X		(X)	(X) (X) (X)		X	(X) (X)			
Stool for Ova, cysts and parasites (Strongyloides) microscopy		X					X				
SUBSET OF PARTICIPANTS RECRUITED TO IMAGING STUDY (HTD Vietnam only)											
Brain MRI		X					X		X		
SUBSET OF PARTICIPANTS RECRUITED TO HYPONATRAEMIA/ICP ANCILLARY STUDY (HTD Vietnam only)											
24-hour fluid balance	(X)	X	X	X	X						
Plasma sodium Plasma osmolality		X	X	X	X						
Urinary sodium Urinary osmolality		X	X	X	X						
Plasma cortisol		X									
Ultra-sound assessment of intravascular volume		X	X	X	X						
Ultra-sound measurement of optic nerve sheath diameter		X	X	X	X						
SUBSET OF PARTICIPANTS RECRUITED TO ADRENAL SUPPRESSION ANCILLARY STUDY (HTD Vietnam only)											
Synacthen test					X (day 21)		X				

### Clinical assessment

Clinical assessment will include conscious level by GCS, new or ongoing focal neurological deficit, clinical treatment response, all serious adverse events including new malignancies and opportunistic infections, all adverse events of any grade leading to modification of anti-tuberculosis treatment or ART or their interruption/early discontinuation (and clinician-assessed likelihood of relationship of adverse event to dexamethasone), and adherence to drugs (study drug, anti-tuberculosis drugs and ART). Assessment of disability by the modified Rankin score will be performed at day 30 from randomisation, monthly until completion of anti-TB drugs, and at months 12, 18 and 24.

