### Protocol treatment discontinuation

An individual participant may stop study drug early for any of the following reasons: Participant no longer believed to have TBM and all anti-tuberculosis treatment stopped; Confirmatory HIV tests are negative and HIV infection excluded; Unacceptable toxicity or adverse event; Intercurrent illness that prevents further treatment; Any change in the participant’s condition that justifies the discontinuation of treatment in the treating physicians opinion and after discussion with the site PI; Inadequate compliance with the protocol treatment in the judgement of the treating physician; Withdrawal of consent for treatment by the participant.

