## Adverse events and safety reporting

### Adverse events

Specific procedures will be followed when notifying and reporting adverse events (AEs) or adverse reactions (ARs). The definitions of the EU Directive 2001/20/EC Article 2 based on the principles of ICH good clinical practice (GCP) apply to this trial protocol. All AEs and ARs will be assessed as to whether they are serious or not. If the event is serious and not only related to TBM, or is fatal, then a serious adverse event (SAE) form must be completed and the OUCRU CTU notified within 24 hours. All AEs and ARs (serious and non-serious) should be graded using toxicity gradings.

Causality of all SAEs or serious adverse reactions (SARs) in relation to the trial therapy (dexamethasone) will be assessed. There are five categories: unrelated, unlikely, possible, probable, and definitely, related. If the causality assessment is unrelated or unlikely to be related, the event is classified as an SAE. If the causality is assessed as possible, probable or definitely related, then the event is classified as an SAR. If there is at least a possible involvement of the trial treatment (or comparator), the investigator must assess the expectedness of the event. An unexpected adverse reaction is one not previously reported in the current Summary of Product Characteristics (SPC) at the time the event occurred, or one that is more frequent or more severe than previously reported. If a SAR is assessed as being unexpected, it becomes a suspected unexpected serious adverse reaction (SUSAR). Investigators should always check the current version of the SPC.

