### Analysis of adverse events

The number of patients with any adverse events and specific events, respectively, will be summarised and informally compared between the two treatment arms based on Fisher’s exact test. The total number of adverse event episodes per patient will also be summarised and informally compared based on a quasi-Poisson regression model with treatment as the only covariate. The following subgroups of adverse events will also be separately summarised: grade 3&4 adverse events; serious adverse events; serious adverse events possibly, probably, or definitely related to the study drug; adverse events leading to TB treatment or ART interruptions. Grade 3&4 laboratory abnormalities will be summarised in the same way as clinical adverse events.

Adverse events due to DILI will be recorded for the DILI study but also for the primary intervention (dexamethasone or placebo). An increased number of adverse events in DILI arms 1 and 2 are not expected, but if they do occur these adverse events will be associated with both the DILI randomisation strategy and for the primary intervention arm in which they occurred.

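### The rule for which non-serious adverse events are recorded is narrower than the planned safety tables, and events that stop the study drug are named in neither

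*Protocol article*

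**What the plan says.** Four sections of the protocol article bear on this point.

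- **Clinical assessment (Data collection).** The adverse-event content of each assessment is all serious events, with new malignancies and opportunistic infections named among them, plus "all adverse events of any grade leading to modification of anti-tuberculosis treatment or ART or their interruption/early discontinuation". The same sentence goes on to record "and clinician-assessed likelihood of relationship of adverse event to dexamethasone), and adherence to drugs (study drug, anti-tuberculosis drugs and ART".
- **Protocol treatment discontinuation.** Study drug may be stopped early for several reasons, one of which is "Unacceptable toxicity or adverse event". No seriousness condition is attached.
- **Adverse events (Adverse events and safety reporting).** "All AEs and ARs will be assessed as to whether they are serious or not", and "All AEs and ARs (serious and non-serious) should be graded using toxicity gradings". Neither statement depends on a change of treatment.
- **Analysis of adverse events.** The main table is described in these terms: "The number of patients with any adverse events and specific events, respectively, will be summarised and informally compared between the two treatment arms". Episodes per patient are also compared. Then: "The following subgroups of adverse events will also be separately summarised: grade 3&4 adverse events". Next come a subgroup for every event that was serious and two narrower ones, given as "serious adverse events possibly, probably, or definitely related to the study drug; adverse events leading to TB treatment or ART interruptions". Laboratory abnormalities of grade 3 or 4 are tabulated as well.

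The Primary aim section makes the safety of dexamethasone part of the main question.

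**The concern.** The drug under test is the one drug not named as a trigger for recording a non-serious event. An event that changes a background tuberculosis drug or ART is listed for collection at any grade and has its own summary. An event that stops only dexamethasone/placebo is not listed for collection unless it is serious, and has no summary of its own at any grade.

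Two things are at stake. First, tables described as covering any event, grade 3 and 4 events and episodes per patient might hold only a subset, without a reader being able to tell. Second, tolerability of the study drug, usually shown by the events that led to stopping it, would not be reported by arm. This also touches the per-protocol analysis of the primary endpoint. That analysis excludes patients who received less than one week of study drug for reasons other than death, so a patient who stops in the first days for non-serious toxicity leaves it, and no listed safety summary would show why.

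**Working it through.** No stated figure depends on this point, so there is nothing to reproduce. The check sets three sections against each other for each kind of event.

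| Kind of event | Clinical assessment | Adverse events | Analysis of adverse events |
|---|---|---|---|
| Serious | Listed | Assessed and graded | Counted; own subgroup; relatedness subgroup |
| Non-serious, interrupts TB drugs or ART | Listed, any grade | Assessed and graded | Counted; own subgroup |
| Non-serious, grade 3 or 4, changes no treatment | Not listed | Assessed and graded | Counted; grade 3 and 4 subgroup |
| Non-serious, lower grade, changes no treatment | Not listed | Assessed and graded | Counted in any-event and episode totals |
| Non-serious, stops study drug only | Not listed | Assessed and graded | Counted, but no discontinuation subgroup; relatedness subgroup excludes it |

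Two results follow.

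1. **Collection against tables.** Rows three to five are counted in the analysis section but are absent from the collection list. The list cannot supply those tables.
2. **Study drug as a trigger.** Row five is the only row that involves a treatment change yet has no matching entry in either list. The omission is not explained by the study drug being out of view: the collection sentence itself mentions dexamethasone for causality and study drug for adherence.

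The consequence depends on which section governs.

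- **If Clinical assessment governs capture,** rows three to five are not recorded as adverse events. The any-event and episode tables then hold serious events plus those that changed TB drugs or ART. A stop of study drug would appear as non-adherence, with no adverse event attached.
- **If the Adverse events section governs,** all five rows are recorded and graded. Clinical assessment then misdescribes collection, sites may work to different rules, and row five still cannot be separated in the planned summaries.

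Under both readings the sections need reconciling, and events leading to study-drug discontinuation lack a summary.

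Scheduled tests cover part of the gap. Fasting glucose and HbA1c are measured at baseline and day 60. By Table 2, dosing ends with week 6 in Grade I (6 × 7 = day 42) and week 8 in Grades II and III (8 × 7 = day 56), so the day-60 measurement falls about 60 − 42 = 18 or 60 − 56 = 4 days after dosing.

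**The case against.** The strongest reply is that Clinical assessment only describes what a visit includes. It contains no word of exclusion and is not the safety section. The Adverse events section is, and it sets the general rule that all events are assessed and graded. Read together, the wider rule holds and the visit list merely highlights items to ask about. Several steroid effects also have their own checks: glucose and HbA1c, day-60 stool examination for Strongyloides, the Synacthen test in a subset, stated monitoring for gastrointestinal bleeding, and malignancy as a secondary endpoint. Finally, this is an article that condenses a longer protocol, and the detail of forms and tables is commonly left to that protocol and the analysis plan.

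Much of this stands. A reader might infer that non-serious events are collected only if they change TB drugs or ART, and that dexamethasone toxicity is therefore under-counted. The document does not establish that, because two sections are wider. A reader might also infer a bias in favour of dexamethasone. The article says dexamethasone may reduce liver injury, so the category that is captured could be one where it looks better. But the collection rule is the same in both blinded arms, and no event rates are given, so the direction is plausible at most.

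What does not stand is the appeal to condensation. The article does not leave the matter open: it states a specific collection list and a specific set of tables, and these disagree. Nor do the scheduled checks replace the missing trigger. Psychiatric effects, for example, have no scheduled check in the article, and a laboratory value does not show that an event led to stopping the drug.

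**Conclusion.** The point holds as an inconsistency and an omission. The inconsistency is that Clinical assessment is narrower than Adverse events and Analysis of adverse events on which non-serious events are recorded. The omission is that events leading to discontinuation of the study drug, which the article allows, are named in neither the collection list nor the analysis subgroups.

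The conclusion that non-serious toxicity stopping only dexamethasone/placebo would go unrecorded as an adverse event rests on one assumption: that the Clinical assessment list is the operative capture rule. The document does not settle this. The size of any under-count cannot be computed, since neither a rate of non-serious toxicity nor a rate of study-drug discontinuation is given, and any patient count would rest on an invented rate. The direction is likewise not derivable.

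The point should be corrected because safety is part of the primary aim and the change is cheap. It does not show that the safety comparison is biased.

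**What to change.** 1. Reconcile Clinical assessment, Adverse events and Analysis of adverse events on which non-serious events are recorded, so that the collection rule supplies the planned tables. At a minimum it should capture all grade 3 and 4 events. If collection stops short of all events, relabel the any-event and episodes-per-patient summaries to say what they contain.
2. In Clinical assessment, extend the trigger to *modification of study drug, anti-tuberculosis treatment or ART*, including interruption and early discontinuation of each.
3. In Analysis of adverse events, add a by-arm summary of adverse events leading to study-drug modification or discontinuation.

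The cost is one case report form item, one extra table and slightly more data entry. Study-drug adherence is already recorded at the same assessments, so no new visit is needed, and no rule on giving or stopping treatment changes.

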### Inpatient assessment

The clinical team will record daily GCS and new focal neurology throughout the participant’s hospital admission. Participants will be visited by one of the research team at screening, baseline, and at least every 3 days for the first 4 weeks of treatment (unless they are discharged or die before 4 weeks) and then at least every 7 days whilst they remain in hospital. Formal trial clinical assessments will occur on day 0, 3, 7, 10, 14, and weekly thereafter until discharge (+/- 1 day).

### Outpatient assessment

After discharge clinical assessments will occur monthly until 12 months. Some of these assessments can be made by phone. Formal outpatient review will occur monthly (+/- 7 days) for at least the first 2 months following hospital discharge. The patient should have formal outpatient review at least every 2 months until month 12 after randomisation. Thereafter patients should be followed up by phone call at 15 months and 21 months and by formal outpatient review at 18 months and 24 months from randomisation.

### HIV monitoring

HIV infection must be confirmed before entry to the study. Peripheral blood CD4 count and HIV viral load will be measured at baseline (routine counts taken within 2 weeks of study entry are acceptable), and CD4 count will be repeated at 60 days.

### Liver function

Alanine transaminase (ALT) and bilirubin will be measured to evaluate liver toxicity every 7 days until discharge.

### Additional blood tests

EDTA blood will be taken for hepatitis B surface antigen and hepatitis C antibodies, and serum will be stored for later DNA extraction where consent has been given. We will use the DNA to investigate novel genetic determinants of treatment response, including LTA4H genotype, and the development of DILI.

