### Ancillary studies

Seven ancillary studies will be conducted within the ACT HIV trial. Some of the studies will only involve a subset of patients recruited at the Hospital for Tropical Diseases (HTD), Ho Chi Minh City, Vietnam. Ancillary studies 2, 3 and 7 will be retrospective data analyses. Ancillary study 4 and 5 will collect and review patient results as the trial progresses. For ancillary study 6 results will be fully analysed at the end of the trial, however laboratory values that may influence clinical care will be available to the clinical team as the trial progresses.

The studies are as follows:

**Ancillary study 1:** A randomised comparison of management strategies in response to DILI (as above). (All patients.)
**Ancillary study 2:** Host and bacterial genetic determinants of treatment response. We hypothesise that the LTA4H gene, and genes involved in related inflammatory pathways, may additionally influence participant inflammatory state, TBM severity, and treatment response. We will also examine genetic variants associated with the development of DILI. (All patients.)
**Ancillary study 3:** Impact of dexamethasone on CSF inflammation and gross cerebral pathology (assessed by serial brain magnetic resonance imaging (MRI)). We will investigate how dexamethasone influences the resolution of inflammatory markers in the CSF and the gross pathological consequences of TBM on the brain (hydrocephalus, stroke, and tuberculoma formation). (HTD patients only.)
**Ancillary study 4:** Influence of diabetes mellitus on presentation and response to treatment. We will investigate whether diabetes mellitus influences clinical presentation and CSF inflammatory phenotype (linking with ancillary study 2), and how it impacts upon treatment outcomes. (All patients.)
**Ancillary study 5:** Influence of Strongyloides infection on presentation and response to treatment. We will determine whether Strongyloides co-infection alters clinical and/or CSF inflammatory phenotype at TBM presentation (linking with ancillary study 2) and treatment response. (All patients.)
**Ancillary study 6:** Pathophysiology and treatment of hyponatraemia and raised intracranial pressure. We will investigate the pathophysiology of TBM-associated hyponatraemia, enabling a better understanding of the causes of hyponatraemia, the relationship between plasma sodium and elevated intracranial pressure, and the best management of severe hyponatraemia. (HTD patients only.)

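### The Additional blood tests section stores serum for DNA extraction while Table 3 lists EDTA blood; the text must be reconciled to protect the genotyping in ancillary study 2

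*Protocol article*

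**What the plan says.** The Additional blood tests section, under Data collection, covers two specimens in one sentence. On hepatitis serology: "EDTA blood will be taken for hepatitis B surface antigen and hepatitis C antibodies". On DNA: "serum will be stored for later DNA extraction where consent has been given". The next sentence gives the purpose: "We will use the DNA to investigate novel genetic determinants of treatment response, including LTA4H genotype, and the development of DILI".

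Table 3, the trial assessment schedule in the same part of the article, groups its blood tests in two blocks. The first reads "EDTA blood for genetic tests Full blood count CD4 count HIV viral load Storage for later DNA extraction". The second starts with sodium, urea/creatinine and liver tests and continues "Hepatitis C antibodies Hepatitis B surface antigen Fasting blood sugar/ HbA1c C-peptide/Lipids Strongyloides serology Serum Storage".

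The DNA feeds ancillary study 2, on host and bacterial genetic determinants of treatment response. For liver injury, the Ancillary studies section says: "We will also examine genetic variants associated with the development of DILI". That study is marked for all patients and is among those to be done as retrospective data analyses.

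**The concern.** The prose and the schedule name different tubes for the same stored material. The difference matters because of what the tubes contain. Whole blood in EDTA keeps the nucleated cells from which host DNA is extracted. Serum is collected after clotting, when those cells have gone with the clot. This is general laboratory knowledge; the documents do not state it. The sentence in Additional blood tests reads as though the two specimen names were transposed.

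If a site worked from that sentence and not from Table 3, the specimen kept for genotyping would be largely cell-free. The fault could also stay hidden for a long time: extraction is to happen later, and ancillary study 2 is analysed retrospectively, so poor DNA might not come to light until after recruitment.

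**Working it through.** The article gives no DNA yield, genotyping call rate or failure rate, so there is no figure to reproduce. The check is a comparison of the passages.

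**1. Specimen for DNA**

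| Place | Specimen named |
|---|---|
| Additional blood tests (prose) | Serum |
| Table 3, first blood block | EDTA blood for genetic tests, with DNA storage in the same block |

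These disagree. The prose is continuous text, and the Table 3 label naming EDTA blood is intact, so the conflict does not come from a broken table.

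**2. Specimen for hepatitis serology**

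| Place | Specimen named |
|---|---|
| Additional blood tests (prose) | EDTA blood |
| Table 3, second blood block | None; the block ends with serum storage |

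Here Table 3 names no tube. The block is mixed: it also holds sodium, fasting blood sugar and HbA1c. Its last entry therefore does not fix the specimen for the hepatitis tests. No explicit contradiction can be shown on this half.

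**3. Are both kinds of sample already scheduled at entry?** The table was flattened in reading, so single marks cannot be tied to single rows with certainty. The counts can be compared:

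- First block: 5 labels (genetic tests, full blood count, CD4, viral load, DNA storage). Marks: 2 at screening + 3 at day 0 = 5.
- Second block: 9 labels (sodium; urea/creatinine; ALT/bilirubin; hepatitis C; hepatitis B; fasting sugar/HbA1c; C-peptide/lipids; Strongyloides serology; serum storage). Marks: 3 at screening + 6 at day 0 = 9.

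The counts match one entry mark per label. On that reading, both the EDTA sample for genetics and the stored serum are already collected at screening or day 0, and correcting the prose adds no draw.

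**4. How far does the problem reach?**

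- Primary endpoint: survival to 12 months. It uses no genotype.
- Randomisation of the main trial: stratified by site and MRC grade, not by genotype.
- Primary analysis: stratified by MRC grade and country. The subgroup and adjustment variables are MRC grade, country, drug resistance, ART status and CD4 count. Genotype is not among them.
- Sample size: 229 deaths and 520 participants, derived from a hazard ratio of 0.69. No genotype input.
- Liver-injury strategy study: its endpoint is the proportion of 60 days without rifampicin and isoniazid. No genotype input.
- Main-trial secondary endpoints: none is genetic.

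Only the genetic work under ancillary study 2 depends on the stored DNA.

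**The case against.** The best defence is that the right sample is already in the plan. Table 3 names EDTA blood for genetic tests under all participants, and sites usually draw blood from a schedule and a laboratory manual, not from a journal paragraph. The article condenses a fuller protocol, specimen handling is normally set out in procedures not shown here, and those may be correct. This defence stands against any claim that samples are actually lost. It does not remove the point: the article does not leave the specimen to another document; it states one, and that statement conflicts with its own schedule.

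A reader might infer more than the documents support:

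- **That DNA is taken from the wrong specimen and the genotyping would largely fail.** This would need sites to follow the prose and disregard Table 3. The prose does not say that EDTA blood is discarded. Any ratio of DNA yield between whole blood and serum would rest on outside cell counts and concentrations, and would not show how likely sites were to use serum.
- **That the prose is the exact reverse of Table 3.** This is explicit for DNA only. For hepatitis serology it is an inference from a mixed block.
- **That genotypes would be lost selectively from participants who die, given planned mortality of 40% to 52%.** If serum were stored for everyone at baseline, the loss would fall on deaths and survivors alike. It becomes selective only if survivors are later re-sampled, a step the article does not describe.

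**Conclusion.** The point holds as an internal contradiction on the specimen for host DNA. The prose in Additional blood tests is the side to correct, because serum is a poor source of genomic DNA and Table 3 already shows a workable sample. The risk is conditional: it applies to sites that act on the prose, and its size cannot be calculated from the documents. The outer limit is the number consenting to DNA storage among the 520 planned participants, and the article does not give that number.

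The consequence is confined to the genetic analyses of ancillary study 2. The main trial's result, its power and the randomised liver-injury comparison do not depend on it. The conclusion rests on one assumption from outside the documents, that serum is largely cell-free. The correction is worth making because it costs almost nothing, while a baseline DNA sample that was never kept may be hard to replace.

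**What to change.** Reword the sentence in Additional blood tests to agree with Table 3: EDTA whole blood taken at baseline is stored for DNA extraction where consent is given. State the specimen for the hepatitis B and C tests as the laboratory procedure specifies it; Table 3 does not settle that, so it should be checked and not assumed to be serum. Then confirm that the laboratory manual, site instructions and tube labels say the same.

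The cost is one sentence and a document check. On the reading of Table 3 above, no extra blood draw is needed, and no change to the analysis or sample size follows.
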